#### 2.2.2. Participants’ Randomization and Personal Data Management

Randomization will be carried out by an independent staff member, who will not be engaged in any other part of the assessment or intervention. For this purpose, a random computer algorithm will be used.

Regarding participants’ personal data, such as name, educational level, etc., the information of each participant will be individually encoded and saved in a locked file cabinet, kept in a separated room from the research laboratory, where the research team will work. Only some members of the research group will handle this information.

### 2.3. Intervention

The 9-month-long intervention, which will be an additional intervention to the conventional care provided by the public health system, as previously described, will include 2 home-based physical exercise 1-hour-long sessions per week for caregivers of relatives with dementia. These physical exercise sessions will be supervised by a physical trainer, who will have an academic degree in sport sciences, and who will be blind to the results of the assessments. Each session will be of home-based, individual and face-to-face nature. While the physical trainer and caregiver are performing the exercise session, the patient might stay at home, either sitting-down doing easy tasks (e.g., watching TV or playing with a pencil and paper-drawing or game task) or carrying out a craft that would be suitable for his/her level of deterioration.

The physical exercise intervention basically consists of aerobic exercises of moderate intensity, which means about 3 to 6 metabolic equivalents. In particular, each physical activity session will consist of: (1) 10-minutes-long warm-up activities that include slight movements of progressive intensity and easy walks and steps. (2) This will be followed by 10-minutes-long aerobic exercises at 60%–65% of maximal heart rate (HR_max_), which will be followed by 20-minute-long overall mobility and strength exercises using own body weight and other materials, which will be followed by a further 10-minute-long aerobic exercise at 60%–65% HR_max_, which will be finally followed by a 10-minute-long cool-down period that includes low-intensity exercises for participants to reach s state of calm.

In order to enhance the attractiveness and the positive effects of the exercises, supplementary materials, such as weights, dumbbells, and elastic bands will be used. During each physical activity session, participants’ heart rate will be monitored by means of a so-called individual running computer (Polar S625X, 1 Polar Electro Oy, Kempele, Finland).

During the 9-months-long intervention, and in order to reinforce other healthy habits in their daily lives apart from physical exercise, participants of the intervention group will be sent a health-counselling document once a month, in which the importance of the following issues will be addressed: adequate rest, safe positioning of the back during caring activities, and regular participation in daily social activities.

During the 9-months-long intervention period, caregivers of the control group will be instructed to continue their normal daily activities. They will also be instructed not to start any new physical exercise program to avoid influencing the study. However, the inclusion criteria of caregivers included no participation in any regular exercise program consisting in 20 minutes’ exercising in the previous 36 months. During the 9-months-long intervention period, participants of the control group will be contacted once a month by telephone in order to conduct an ad hoc standardized, non-exercise-related conversation with a member of the researcher team, in order to remind them of the conditions of the study.

### 2.4. Measures

Participants of both groups will be evaluated at home by trained members of the research team at baseline, 3 and 9 months after the intervention and at follow-up (12 months after the intervention). Each of the four evaluations will last 45 minutes. Prior to the baseline evaluation, and in order to apply a standardized evaluation protocol, the evaluators will be given a testing manual that has been ad hoc written by the research team. This manual contains the description and particular instructions for all assessment procedures. They will also participate in an assessment-training workshop that consists of 3 sessions, each 3–4 hours-long. This training workshop will be focused on improving evaluators’ skills to apply the protocol properly. The evaluators will be instructed to learn the particular procedures for implementing the questionnaires, and they will train their skills to perform the selected fitness tests and to proceed with the participants (e.g., how to prepare the session in a small room instead of a gym, avoiding interaction with the Alzheimer’s patient as previously described, or how to chat about other issues of society or needs of the caregiver to distract them from caring). This training will be supervised by the head of the research team.

All of the evaluation tools have been shown to have a moderate to high reliability and validity in samples of old people and caregivers.

#### 2.4.1. General Measures

Socio-demographic and other data from the caregivers will be compiled using a questionnaire that has been made ad hoc for this purpose. The compiled demographic data will include age, place of residence, marital status, number of co-residents, educational level, smoking and alcohol consumption habits, and level of physical activity. Other data will include the nature of the relationship with regard to the relative with dementia, as well as the number of years spent caring the relative with dementia.

Regarding the relatives with dementia, the number of years since diagnosis of dementia, as well as the functional status, will be evaluated by the trained member of the research team using the Barthel Index [70]. This 10-item measure assesses the care-recipient’s capacity to perform 10 basic activities of daily life, such as the ability to dress or bathe. Numerical scores are assigned according to whether the individual requires assistance to perform the task or whether he/she is able to do the activity independently. This will provide a quantitative estimation of the individual’s level of dependency, ranging from 0 to 100. Higher scores indicate a higher level of independence, and the opposite pattern is indicated by lower scores.

#### 2.4.2. Analysis of the Effects of the Intervention

As we have previously described, all participants will complete all evaluation procedures at baseline and at 3 and 9 months after the intervention and at follow-up (12 months after the intervention). During the 9-months-long intervention, data regarding participants’ use of public and private health services will be compiled. In particular, information will be compiled on hospital stays, medication and secondary and primary health-care appointments.

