### 2.2. Participants

Participants will be recruited in cooperation with regional supporting associations for relatives of individuals with dementia. Potential participants will be identified and screened for eligibility in accordance with the study inclusion and exclusion criteria by trained members of the research team. The inclusion criteria will be: being a female caregiver of a relative with dementia; living at home with the patient with dementia; providing the relative with dementia with at least 20 hours of unpaid in-person care per week; being age 50 years or older; having no medical condition that could limit participation in a moderate-intensity exercise program; not having participated in any regular physical activity program, that is, having been engaged in less than two 20-minutes-long sessions of exercise per week during the 36 months prior to the intervention; not having changed medication or doses of medication for at least 3 months prior to study; and not having plans to move from the place of residence within the 12-month-long study. The exclusion criteria will be: having any external economic or personal support for caregiving of the patient with dementia. A written copy of the study protocol will be sent to all potential participants. In addition, at the first session of assessment, participants’ potential doubts will be solved by the member of research team. A signed informed consent will be requested to participate from all eligible participants prior to inclusion in the study.

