#### Cost Utility Analysis

This analysis will be performed in two steps. First, the incremental mean costs of the exercise-based program, and the mean increase in QALYs secondary to the program, will be estimated using a health-care perspective. Second, the incremental cost-effectiveness ratio for the intervention will be calculated by dividing the incremental costs by the incremental QALYs.

To report uncertainty due to sampling variation, the 95% confidence interval will be calculated using the non-parametric bootstrapping technique (1000 replicates re-sampled with replacement from treatment and control populations), and a cost-effectiveness acceptability curve will be plotted [73,74]. This curve shows the probability that the intervention is cost-effective compared with the alternative across the range of values that decision makers are willing to pay to achieve an additional QALY. The “investment ceiling” is the maximum possible level of spending, even under the assumption of unlimited funding availability. For the health-care system in Spain, the current year adjusted investment ceiling was set at a conservative €30,000/QALY (30000 to 50000 E/QALY is normally accepted).

Decision makers should compare this upper limit of acceptable payment with estimated incremental cost-effectiveness ratios, to determine whether a given treatment is cost-effective relative to the alternatives.

A range of sensitivity analyses will be performed to explore the robustness of the estimates and to determine how dependent the results will be on estimates of participants’ unit costs and efficacy. The first analysis will examine the influence of participation rate in the program, as this could influence productivity by affecting the number of participants per unit of time provided by the personal trainer. A second analysis will explore the effects of cost fluctuations that might be take place due to changes in the salary of the physical trainer, since this is a major source of variability in economic studies [75]. The time and cost of travel from the research center to the participant’s residence will also be calculated. Finally, the robustness of cost utility will be assessed by analyzing different possible scenarios, combining the influence of variations in staff salary, rate of participation, distance to the participant’s home, and effectiveness, ranging from the lowest to the highest limit of the 95% confidence interval.

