## 3. Outcomes

### 3.1. Primary Outcomes

#### 3.1.1. Health-Related Quality of Life and Cost-Utility

The main purpose of the analyses is to assess the cost-effectiveness of the targeted intervention, which is an intervention added to the conventional care. Therefore, the primary outcome will be the Spanish time trade-off utility of EQ-5D-3L (EQ-5D-3L utility) in terms of QALYs. The EQ-5D-3L [76] will be used to assess the general health status and the five dimensions of health-related quality of life: (1) mobility, (2) self-care, (3) daily activities, (4) pain and discomfort, and (5) anxiety and/or depression of participants. Each dimension is rated using a 1 to 3 level scale, where 1 = no problem, 2 = some problems and 3 = extreme problems. Using a combination of these different dimensions, it is possible to identify a total of 243 possible health states. At the end of the screening, we will obtain a total score of utility that will range from 1 = fully functional quality of life to 0 = death [77]. Participants’ data regarding the QALYs compiled 9 months and 12 months after the intervention will be used to make comparisons between the intervention group and the control group. In this way, we will be able to find potential differential changes in the QALYs of the participants as a function of whether they were subjected to the intervention or not. For this purpose, participants’ health utility curves will be calculated and compared among participants of both sample groups. We include a 12-months-long follow-up period, following the recommendations of the National Health Service (NHS). To avoid bias, data will be adjusted for differences in baseline EQ-5D scores via regression analysis [78].

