##### Cost-Utility: Cost Units

Since the study intervention is home-based, the intervention will have no direct impact on societal costs, such as travel expenses or the time spent by the caregiver at home, but the possible reduction of health visits to physician or nursery could vary. However, variation in travel costs (time and transport) of the initial visit to participants’ homes to explain the study and to evaluate the caregivers will be included in the sensitivity analysis. The economic analyses will be performed from a health service perspective, as recommended by the National Institute for Clinical Excellence (NICE) in the UK to inform decisions concerning health-care policy for an expensive condition. This may help to determine whether the addition of the program to the health system should be funded. The unit costs will be expressed in Euros (€) in the current year of intervention.

No adjustment will be required for changes in currency value over time, as the study will focus on effects observed over a period of ≤1 year. The costs of the program will be calculated on the basis of: university graduate salary levels; personnel costs for the running of the program; public-sector mileage rates; and the private external management costs of the program (insurance, basic portable sport materials, e.g., strings and step-equipment). Health-care prices (consultations, etc.) will be based on the official bulletin of the regional government of Extremadura. Drug prices will be obtained from the Spanish version of the Vademecum International [79].

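### Health-service use is stated for the 9-month intervention only, QALYs are compared at both 9 and 12 months, and the ICER has no named horizon

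*Protocol article*

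**What the plan says.** Four places in the protocol article bear on this.

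- **Cost window.** Section 2.4.2 first lists all four assessments, including the 12-month follow-up. It then gives service use its own, shorter window: "During the 9-months-long intervention, data regarding participants’ use of public and private health services will be compiled". The items are named: "information will be compiled on hospital stays, medication and secondary and primary health-care appointments".
- **QALY window.** Section 3.1.1 makes EQ-5D-3L utility, expressed as QALYs, the primary outcome and says that "data regarding the QALYs compiled 9 months and 12 months after the intervention will be used to make comparisons". The same paragraph gives a reason for including a 12-month follow-up.
- **ICER.** The Cost Utility Analysis section says that "the incremental cost-effectiveness ratio for the intervention will be calculated by dividing the incremental costs by the incremental QALYs". It names no time horizon.
- **Time frame.** The section on cost units says only that "the study will focus on effects observed over a period of ≤1 year", which fits either 9 or 12 months.

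Service use does enter the cost side. The section on cost units takes a health-service perspective, gives price sources for consultations and drugs, and expects that the number of health visits may change.

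**The concern.** The incremental costs and incremental QALYs in an ICER must cover the same period. Followed as written, the plan has QALYs to month 12 but health-service costs to month 9. If the ICER is taken at 12 months, any between-arm difference in consultations, hospital stays or medication after the programme ends is treated as zero, while the QALYs of those months are counted.

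The protocol itself expects that the programme may change service use, so a zero difference after month 9 cannot simply be assumed. The listed sensitivity analyses vary participation, trainer salary, travel and effectiveness. None varies the amount of service use or the horizon, so none would show the gap. Section 3.1.1 calls cost-effectiveness the main purpose of the analyses, so the point touches the central result.

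**Working it through.** **Inputs from the protocol article**
- Programme cost: EUR 1680 per caregiver (section 2.2.1), for a 9-month intervention.
- Threshold: EUR 30,000 per QALY (sections 2.2.1 and Cost Utility Analysis).
- QALY gain used in sizing: 0.06 (section 2.2.1).
- Service-use window: 9 months (section 2.4.2). QALY comparisons: 9 and 12 months (section 3.1.1).
- Study length: the eligibility criteria in section 2.2 include "not having plans to move from the place of residence within the 12-month-long study". Month 12 is therefore counted from baseline.

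**The plan's own figure.** The plan states no ICER. The nearest figure is the QALY gain, which reproduces as the break-even gain: 1680 / 30,000 = 0.056, rounded to 0.06.

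**Length of the gap.** 12 - 9 = 3 months, or 3/12 = 25% of a 12-month horizon. This is 25% of the time, not of the cost, because the programme cost falls wholly within the first 9 months.

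**Size of the error.** Let m be the between-arm difference in health-service cost (intervention minus control, EUR per caregiver per month), assumed constant. Then:
- stated costs, to month 9: 1680 + 9m
- matched costs, to month 12: 1680 + 12m
- both are divided by the same 12-month QALY gain, which cancels, so relative error = (1680 + 9m) / (1680 + 12m) - 1

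The documents give no value for m, so a range is assumed:

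| m (EUR/month) | Costs to month 9 | Costs to month 12 | Error in 12-month ICER |
|---|---|---|---|
| -50 | 1230 | 1080 | +13.9% |
| -20 | 1500 | 1440 | +4.2% |
| 0 | 1680 | 1680 | 0% |
| +20 | 1860 | 1920 | -3.1% |
| +50 | 2130 | 2280 | -6.6% |

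If the programme saves service use, the mismatched ICER is too high; if it adds service use, too low.

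**Effect of the unnamed horizon.** This is a trapezoid area under an assumed between-arm utility difference that starts at 0 at baseline and peaks at 0.10, with m = 0:

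| Assumed path | Difference at months 3, 9, 12 | QALYs to 9 | QALYs to 12 | Share from months 9-12 | ICER at 9 | ICER at 12 |
|---|---|---|---|---|---|---|
| Early gain, held | 0.10, 0.10, 0.10 | 0.0625 | 0.0875 | 29% | 26,880 | 19,200 |
| Early gain, fades | 0.10, 0.10, 0 | 0.0625 | 0.0750 | 17% | 26,880 | 22,400 |
| Gradual gain, held | 0.033, 0.10, 0.10 | 0.0375 | 0.0625 | 40% | 44,800 | 26,880 |
| Gradual gain, halves | 0.033, 0.10, 0.05 | 0.0375 | 0.05625 | 33% | 44,800 | 29,867 |

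First row: 0.25 x 0.05 + 0.5 x 0.10 = 0.0625; adding 0.25 x 0.10 gives 0.0875; 1680 / 0.0875 = 19,200.

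On these paths months 9 to 12 supply 17% to 40% of the 12-month gain. On the two gradual paths, the 9-month and 12-month ICERs fall on opposite sides of EUR 30,000.

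Combining the four paths with the five values of m, missing costs alone carry the 12-month ICER across the threshold in 2 of 20 cases. One is the early-gain-then-fade path at m = +50: 28,400 with costs to month 9, 30,400 with costs to month 12. The other is the gradual-gain-held path at m = +20: 29,760 against 30,720.

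**The case against.** The strongest reply is that a 9-month ICER fits every section. The ICER definition names no horizon, section 2.5 analyses change over the 9-month intervention, and the 12-month visit could serve only to see whether effects last. Costs and QALYs would then match and nothing would be wrong. This stands as far as it goes: a reader might infer that the planned ICER divides 9-month costs by 12-month effects, and the document does not say so. What remains is that the plan also compares QALYs at 12 months, gives a reason for that follow-up, and states no cost collection to go with it.

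A second reply is that section 2.4.2 does not exclude later collection, and that an article may leave data forms to the full protocol. That is fair, so one cannot claim that the data will certainly not exist. But the article does more than stay silent: it states a window, and the window is shorter than the follow-up.

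Two larger sizes are tempting and do not hold.
- Some sections literally place the last visit 12 months after the intervention. A reader might infer a 21-month study with 12 of 21 months (57%) uncosted. That conflicts with the 12-month study length in section 2.2 and the limit of one year in the section on cost units.
- From 30,000 x 0.06 - 1680 = EUR 120, a reader might infer a margin so thin that any unrecorded difference above EUR 120 reverses the conclusion. That margin comes from rounding: at the unrounded 0.056, net benefit is 30,000 x 0.056 - 1680 = 0. The figure is the break-even gain, not a forecast, so it says nothing about the expected margin.

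**Conclusion.** The point holds in a limited form and should be fixed. The stated service-use window does not cover the 12-month QALY comparison, and the ICER horizon is not named. Followed as written, the plan supports a matched 9-month ICER but not a matched 12-month one.

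The gap is 3 months, with month 12 counted from baseline. It affects only the between-arm difference in service use over those months. Its sign is unknown, it is zero if the arms do not differ, and it is about -7% to +14% of the ICER for assumed constant differences of +50 to -50 EUR per caregiver per month. That range and the utility paths are assumptions; the documents supply neither.

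**What to change.** 1. In the Cost Utility Analysis section, state one base-case horizon that applies to both costs and QALYs.
2. To support the planned 12-month QALY comparison, give the same service-use form to both arms at the existing 12-month visit, covering months 9 to 12, and amend section 2.4.2 to say so.
3. Report the matched 9-month ICER (costs and QALYs both to month 9) alongside.
4. State in sections 2.1, 2.4 and 3.1.1 that visit months are counted from baseline, so that the gap cannot be read as longer.

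The cost is one short recall form at a planned visit and a few words of protocol text. If the investigators intend a 9-month base case, naming it makes that ICER matched with no new data; a 12-month ICER would still need the form.

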### 2.5. Data Statistical Analysis

To determine possible inter-group differences in baseline data, the mean values of all baseline variables will be analyzed using independent sample t-tests. Moreover, for continuous variables with a normal distribution, we will use the Kolmogorov–Smirnov test and the correction of Lilliefors. For categorical variables, in turn, we will use the Pearson’s chi-squared test. In addition, inter-group differences will be analyzed using the Mann–Whitney U-test for continuous variables and the χ^2^ test for categorical variables. An analysis of variance will be also performed to determine inter-group differences regarding potential changes in the measured variables over the 9-months-long intervention period. Possible confounding factors, such as age, subjective burden, caregiver-rated Barthel Index, and length of caregiving-history at baseline, will be treated as dependent covariates. To determine the magnitude of change, effect sizes will be calculated using the pre-post-control (PPC) design [71]. The use of repeated measurements in the PPC design allows data from each individual to be used as his or her own control data, which typically increases the power and precision of statistical tests [72]. To determine the variable that best describes and predicts changes in different parameters, an adjusted multiple regression analysis will be performed. For all tests, the significance level will be set at *p* < 0.05. All statistical calculations will be performed using SPSS 18.0 (SPSS Inc., Chicago, USA).

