#### 2.2.1. Sample Size Calculation

The required sample size will be estimated using the utility score of the Spanish version of the EQ-5D-3L questionnaire as primary outcome, and taken into account that this is an experimental study that will compare two groups with a significance level alpha = 0.05 and 80% of the statistical power that is required to detect a minimal clinically significant difference of 0.20 and SD = 0.12 [68].

On the other hand, we have also to consider the costs of the intervention added to the conventional care provided by the public health system, which will be 1680 € per caregiver. This amount will include the personal trainer’s salary, insurance, and 2 h/week travel-related costs.

A third aspect refers to the cost-efficiency ratio expressed as cost per quality-adjusted-life-years (QALYs). This will range between 10,000 and 50,000 € per QALYs [69], and we will use a conservative estimated sum = 30,000 € per QALYs. A cost-efficiency ratio = 0.21 corresponds to a 0.06 QALYs. In view of the above, a sample size of n = 50 caregivers distributed in two groups—control group and intervention group—is required to achieve a statistical power of 80% with a 95% of confidence interval, using an analysis of variance in parallel to parametric testing and anticipating a potential drop-out rate of 20%. In addition, in order to improve the confidence interval, a bootstrapping technique will also be used.

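### Section 2.5 calls its baseline covariates 'dependent', names no own-baseline covariate for depression, SCL-90-R or fitness, and gives no rule between Mann–Whitney and ANOVA

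*Protocol article*

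**What the plan says.** Section 2.5 (Data Statistical Analysis) of the protocol article sets out these steps in order:

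- Baseline comparison: "the mean values of all baseline variables will be analyzed using independent sample t-tests". A normality test and a chi-squared test follow.
- Then, as an addition, "inter-group differences will be analyzed using the Mann–Whitney U-test for continuous variables". The text does not say whether this concerns baseline values or treatment effects, and it does not link the choice to the normality test.
- Then the effect analysis over the nine months: "An analysis of variance will be also performed to determine inter-group differences regarding potential changes in the measured variables".
- Adjustment: "Possible confounding factors, such as age, subjective burden, caregiver-rated Barthel Index, and length of caregiving-history at baseline, will be treated as dependent covariates".
- Magnitude: "effect sizes will be calculated using the pre-post-control (PPC) design".
- Prediction of change: "an adjusted multiple regression analysis will be performed", with no adjustment set named.

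A threshold of 0.05 applies to every test, and no test is named as primary.

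Section 3.1.1 adds, for the utility outcome: "To avoid bias, data will be adjusted for differences in baseline EQ-5D scores via regression analysis". Sections 3.1.2 to 3.1.5 place burden, depression, SCL-90-R and fitness under the same primary-outcomes heading, without a comparable sentence.

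**The concern.** Three things in section 2.5 need correction or a decision.

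1. A dependent variable is an outcome. Taken literally, the sentence on confounders puts baseline factors where they can adjust nothing.
2. The baseline value of an outcome is usually among its strongest predictors, and it is collected here for every outcome. Section 3.1.1 uses it for EQ-5D, and the list in section 2.5 happens to include it for burden. For depression, SCL-90-R and fitness no passage names it. Analysing change, or standardising it in a pre-post-control effect size, uses the baseline but does not adjust for it in the ANCOVA sense, and precision is lost. In a trial of 50 caregivers that loss matters.
3. If Mann–Whitney is an effect test, each continuous outcome has two group comparisons and no rule for which one counts. The list of confounders is also open, so the adjusted model can be settled after the results are seen.

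**Working it through.** **Inputs.** From section 2.2.1: 50 caregivers in two groups, "anticipating a potential drop-out rate of 20" per cent, so 50 × 0.80 = 40 evaluable, or 20 per arm if allocation is 1:1 (the ratio is not stated). The baseline–follow-up correlation r is not given. It is an assumption here, with range 0.3 to 0.8. The plan gives no precision figure for these outcomes, so there is none to reproduce, and nothing below rests on how the 50 was derived.

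**Which outcomes have a named own-baseline covariate.**

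| Outcome | Own baseline named? | Where |
|---|---|---|
| EQ-5D utility / QALY | Yes | 3.1.1 |
| Burden (ZBI) | Yes, through the listed factor | 2.5 |
| Depression (GDS-15) | No | – |
| SCL-90-R | No | – |
| Fitness measures | No | – |

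**Precision.** Take equal variance σ² at baseline and follow-up, and correlation r.

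- Change score: Var = 2σ²(1 − r)
- ANCOVA residual: Var = σ²(1 − r²) = σ²(1 − r)(1 + r)
- Ratio, change to ANCOVA: 2/(1 + r)

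The ANCOVA sample that gives the same precision as 40 caregivers on change is 40 × (1 + r)/2.

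| r (assumed) | Ratio 2/(1+r) | 40 on change are worth, under ANCOVA |
|---|---|---|
| 0.3 | 1.54 | 26 |
| 0.5 | 1.33 | 30 |
| 0.6 | 1.25 | 32 |
| 0.7 | 1.18 | 34 |
| 0.8 | 1.11 | 36 |

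The comparison is with an unadjusted change score. Any precision gained from age, burden, Barthel Index or length of caregiving is not counted.

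**Free choice of test.** Null data were simulated with 20 and 25 per arm, r = 0.5 and 0.7, and normal and skewed (log-normal type) distributions. There were 6,000 runs per scenario, and the Monte Carlo standard error at 5% is √(0.05 × 0.95/6000) ≈ 0.3 percentage points. Rejection rates at p < 0.05 across the eight scenarios:

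| Analysis | Type I error |
|---|---|
| ANOVA on change alone | 4.4–5.0% |
| Mann–Whitney on follow-up alone | 4.4–5.1% |
| ANCOVA alone | 4.3–5.3% |
| Better of ANOVA and Mann–Whitney, both on change | 5.7–7.1% |
| Better of ANOVA on change and Mann–Whitney on follow-up | 8.1–9.2% |

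Any one fixed test holds the level. Choosing between two does not, and the excess depends on which values Mann–Whitney is applied to.

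**The case against.** The strongest reply is that this is a language slip in a condensed article. The same sentence speaks of confounding factors and covariates, so adjustment is plainly intended. The list is illustrative, so other baselines are not excluded. Per-outcome model terms are often left to an analysis plan. An ANOVA of change is also valid in a randomised trial: it loses precision but introduces no bias. The Mann–Whitney sentence stands among the baseline comparisons and can be read as their non-parametric counterpart.

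Much of this stands. The intent to adjust is clear, the loss is one of precision, and the Mann–Whitney reading is open. What remains is that the stated term is wrong, that two sections of one document give different adjustment sets, and that the side-by-side tests carry no rule.

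Three stronger readings are tempting, and the text does not support them:

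- *That own baseline is omitted throughout.* Section 3.1.1 adjusts EQ-5D for it, and baseline burden is in the section 2.5 list.
- *That t-tests compete as effect tests.* Section 2.5 confines them to baseline data.
- *That a repeated-measures ANOVA will delete every caregiver with a missed visit.* Section 2.5 names neither that model nor complete-case deletion. Its mention of repeated measurements describes the effect size, and a change from baseline to nine months does not need the three-month visit.

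**Conclusion.** The point holds in a limited form. 'Dependent' is an error and should be corrected. For depression, SCL-90-R and fitness, three of the five headings under primary outcomes, no own-baseline adjustment is named. An unadjusted change-score analysis would there carry 1.11 to 1.54 times the variance of ANCOVA. That range assumes r between 0.8 and 0.3 and equal variances, and it is an upper guide because the other planned covariates may recover part of the loss. It does not apply to EQ-5D or burden. The type I error of about 6–9% is conditional on Mann–Whitney being an effect test and on the better result being reported. If it is a baseline test only, that part falls away. A reader might conclude that the effect estimates will be biased or that the primary utility analysis is unadjusted; the document supports neither.

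**What to change.** Amend section 2.5 in three places:

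1. Replace 'dependent' with independent, prespecified covariates, and close the list by removing the wording that makes it illustrative.
2. Extend the own-baseline adjustment of section 3.1.1 to every continuous outcome: ANCOVA with group and the outcome's baseline value, plus the closed list of named factors. The ANOVA on change can be kept if preferred. Once the outcome's own baseline is in the model, the group estimate is the same whether change or follow-up is the response.
3. Name this as the single primary effect analysis, and give Mann–Whitney a stated role, either as a sensitivity analysis or for baseline description only.

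A different model class, a cap on the number of covariates, or removal of the baseline tests is not needed to resolve this point.

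The cost is small. No new data are required, and there is slightly more analysis work. With about 40 evaluable caregivers, a model with intercept, group, own baseline and all four named factors leaves 40 − 7 = 33 residual degrees of freedom.
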